## Methods

### Study design

The design of the study is a randomized controlled, cross-over trial. The study will follow the Standard Protocol Items: Recommendations for Interventional Trials (SPIRIT) guidelines for the design and conduct of a trial (Fig. 1; Additional file 1) [53]. As outlined in Fig. 2, participants will be asked to visit the Movement Physiology Research Laboratory on five occasions; the first visit will be for screening the volunteers to ensure that they fit the study criteria. Thereafter, eligible participants will return to the laboratory before the start of, and after, each dietary intervention. Following 1 week of normal habitual dietary monitoring, each participant will follow two isocaloric diets (a KD and a high-carbohydrate, low-fat (HCLF) diet) in a randomized order and separated by a 1-week washout period. Randomization of the order of the diets will be done using the Microsoft Excel 2010 (Version 14.0) CHOOSE and RANDBETWEEN functions. These functions (=CHOOSE(RANDBETWEEN(1,2), “A”,“B”) are able to assign each new participant into one of the two diets. Each dietary intervention will last for a minimum period of 3 weeks. In the KD it is critical for the participant to remain in a ketogenic state for three consecutive weeks. Should the participant leave the ketogenic state (as assessed by blood ketone levels), the dietary intervention period will be prolonged until the consecutive, 3-week ketogenic state is achieved. If a participant does not reach a ketogenic state in 2 weeks, we will exclude them, as it is indicative of non-compliance. However, we will be more lenient with someone who has entered a ketogenic state but may struggle to maintain the state, in which case we will guide them by closely monitoring their diet to ensure that their carbohydrate intake is suitably low and that their fat intake is suitably high. We will also look at the content of each participant’s diet to ensure that the foods do not contain imperceptible carbohydrates or that their protein content is not too high, which may result in gluconeogenesis. We will continuously encourage pure fat intake, e.g., cooking with olive oil, butter or coconut oil. Should a participant leave the ketogenic state more than five times they will be excluded from the study.

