#### Laboratory assessments

Before and after each dietary intervention (i.e., four times), participants will return to the laboratory after an overnight fast, for anthropometric measurements and to provide a blood sample. Tests to assess cognitive function tests and BMR will also be assessed at each of these visits, and validated and standardized Pittsburgh Sleep Quality Index (PSQI) [55] questionnaires will be administered to assess sleep quality.

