### Outcomes

All outcomes will be measured at baseline, and before and after 3 weeks of each dietary intervention. The primary outcome will be diet-induced change in sleep quality, cognitive function, markers of inflammation and cardiovascular health status. The secondary outcomes will be a change in BMR and thyroid function.

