### Data analysis

Data analysis will be done using IBM SPSS Statistics (version 24, IBM Corporation, NY, USA). A two-tailed statistical significance will be accepted at *P* < 0.05. Each outcome variable assessed will be analyzed according to diet (KD or HCLF) and time (before and after each diet) using a repeated-measures two-way analysis of variance (ANOVA). Where appropriate, a Student-Newman-Keuls post-hoc test will be used to assess the origin of any significant differences detected by the ANOVA models. Variables will be adjusted for potential confounders which will be determined using multiple linear regressions. A power analysis has indicated that total of 20 participants would provide 85% power to obtain a medium effect size for BMR (Cohen’s *d* effect size = 0.3) [54].

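### The diet-by-time ANOVA subtracts the 'before' values at a fixed weight of 1 instead of adjusting for them, which can cost precision with 20 participants

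*Protocol article*

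**What the plan says.** The Data analysis section fixes one model for all outcomes. Each is to be "analyzed according to diet (KD or HCLF) and time (before and after each diet) using a repeated-measures two-way analysis of variance", with the significance rule "A two-tailed statistical significance will be accepted at *P* < 0.05". The Outcomes section defines the target as a change: "The primary outcome will be diet-induced change in sleep quality, cognitive function, markers of inflammation and cardiovascular health status". BMR and thyroid function are secondary and are also defined as changes.

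The design is a two-diet cross-over, with the diets taken "in a randomized order and separated by a 1-week washout period". Laboratory values are available at four visits per person: "Before and after each dietary intervention (i.e., four times), participants will return to the laboratory after an overnight fast".

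On covariates there is one sentence: "Variables will be adjusted for potential confounders which will be determined using multiple linear regressions". It does not mention the 'before' value.

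**The concern.** In a cross-over each participant is already their own control, so the KD–HCLF difference in the 'after' values is free of the stable person level. The diet-by-time interaction then subtracts a second within-person difference, that of the two 'before' values, and adds its noise to the contrast. The subtraction pays off when that difference predicts the 'after' difference with a slope near 1. When the slope is well below 1, it costs precision.

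With 20 participants and two-sided 5% tests, such a loss would make inconclusive results more likely on every outcome analyzed this way, although the values needed to avoid it are already collected.

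**Working it through.** **Inputs.** From the article: 20 participants (Participants; Data analysis), two-sided 0.05, four visits per person, and the diet-by-time model. Assumed, because the article does not give them: r and k, defined below.

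**The article's own figure.** The Data analysis section states that a "total of 20 participants would provide 85% power to obtain a medium effect size for BMR (Cohen’s *d* effect size = 0.3"). A paired t-test with a standardized difference of 0.3 and n = 20 has 24.7% power. To reach 85% at d = 0.3, an 'after'-only comparison would need a within-person correlation of about 0.91, and the interaction about 0.955 (all visits equally correlated). Neither is stated. So the power statement does not reproduce from its stated inputs and cannot be used to infer r. That is a separate matter, and nothing below depends on it.

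**Notation.** For each participant:
- D_A = after-KD − after-HCLF
- D_B = before-KD − before-HCLF
- r = Corr(D_A, D_B)
- k = Var(D_B)/Var(D_A), with Var(D_A) set to 1

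**Step 1: the planned test.** The 2 × 2 interaction is a one-sample t-test of D_A − D_B. Its variance is 1 + k − 2r√k.

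**Step 2: the baseline-adjusted test.** Regress D_A on D_B and test the intercept. The residual variance is 1 − r². Estimating the slope inflates the intercept's variance by 1 + 1/(n − 3) = 1 + 1/17 = 1.059.

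**Step 3: the ratio, planned to adjusted.** Since (1 + k − 2r√k) − (1 − r²) = (√k − r)²,

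ratio = [1 + (√k − r)²/(1 − r²)] / 1.059.

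The optimal slope is r/√k. The planned test is efficient only when this is near 1, that is, when r is near √k. There the ratio reaches its minimum, 1/1.059 = 0.944, so adjustment can lose at most about 5–6%.

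| r | k = 1 | k = 0.75 | k = 0.5 |
|---|---|---|---|
| 0 | 1.89 | 1.65 | 1.42 |
| 0.25 | 1.51 | 1.33 | 1.15 |
| 0.5 | 1.26 | 1.11 | 1.00 |
| 0.75 | 1.08 | 0.97 | 0.95 |
| 0.85 | 1.02 | 0.95 | 1.01 |

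Example, k = 1 and r = 0.5: (1 − 0.5)²/(1 − 0.25) = 0.333, and 1.333/1.059 = 1.26.

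**Step 4: break-even.** At k = 1, (1 − r)/(1 + r) = 1/17 gives r = 16/18 = 0.89. This threshold holds only for equal variances. At k = 0.5 the adjusted analysis is slightly worse from r of about 0.50 to 0.84.

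**Step 5: power, for k = 1 only.** At an effect for which the adjusted analysis has 80% power, the planned test has about 53%, 63%, 71%, 77% and 79% at the five values of r (non-central t). To match the adjusted analysis it would need 20 × ratio, or about 38, 30, 25, 22 and 20 participants.

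**Step 6: is a small r plausible?** Let the before–after correlation within a diet period be w, and let every correlation across periods be b. Then r = (w − b)/(1 − b). If all four visits are equally correlated, r = 0 however high that correlation is. With w = 0.85 and b = 0.70, r = 0.15/0.30 = 0.5. The two visits of one diet period are at least 3 weeks apart. The end of the first period and the start of the second are separated only by the 1-week washout. A small r is therefore possible, but the article does not establish it.

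**The case against.** **The planned test is valid and matches the outcome.** This stands. Without carry-over and with randomized order, D_B has expectation zero, so both analyses estimate the same diet effect and both hold the 5% level. A reader might infer that the ANOVA is biased or answers the wrong question. Nothing in the article supports that.

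**The size rests on quantities not in the article.** This also stands. A reader might conclude that the plan gives away half of the trial's precision. The largest figure in the table, 1.89, is a 47% loss (1 − 1/1.89) and needs r = 0 together with equal variances. Both 'before' visits follow a week of habitual diet, while the 'after' visits follow two very different diets. If people respond differently to the diets, the 'after' differences vary more, k falls below 1 and the gain shrinks or turns slightly negative.

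**The confounder sentence may cover it.** This stands in part. Baseline is neither named nor excluded, so one cannot say that it will never be used. But covariates chosen from the data by regression are not a prespecified adjustment, and the article itself fixes the model in which 'before' is a level of the response.

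**'After' values alone would do.** Not in general. With equal variances 'after'-only is slightly better at r = 0 (simulated power 85% against 83% for the adjusted test), but above r = 0.5 it is less precise than even the planned contrast.

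**Conclusion.** The point holds as one of efficiency. The article's model tests the raw difference of changes and does not name the 'before' values as covariates. With 20 participants its variance relative to a baseline-adjusted contrast runs from 1.89 (r = 0) to 1.02 (r = 0.85) under equal variances, and from 1.42 down to about 0.95 when the 'before' difference has half the variance of the 'after' difference. Adjustment can therefore save a good deal and lose at most about 5–6%. That asymmetry, with the data already in hand, is the reason to change the plan.

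The conclusion assumes no carry-over across the washout and approximately normal differences. r and k are assumptions throughout.

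**What to change.** In the Data analysis section, prespecify for each outcome a regression of (after-KD minus after-HCLF) on (before-KD minus before-HCLF), with the intercept as the estimate and test of the diet effect. The 'before' difference must be left uncentred: centring it at its sample mean turns the intercept back into the unadjusted 'after' difference. Keep the diet-by-time table as description.

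If a mixed model for the two 'after' values is preferred, either make participant a fixed effect or include the person-mean 'before' value as well. A random-intercept model with only each diet's own 'before' value is not equivalent, because its slope mixes between-person and within-person information. In simulation with all four visits correlated at 0.8 (so r = 0) and n = 20, its variance was about 1.5 to 1.6 times that of 'after'-only, against 1.03 to 1.07 for the difference regression and about 2 for the planned contrast.

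Cost: one sentence, no new data or visits, and one degree of freedom. About 5–6% of precision is lost when adjustment adds nothing over the planned contrast.

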### Participants

Twenty healthy individuals, between the ages of 18 and 50 years, will be asked to volunteer in this study. A total of 20 participants would provide 85% power to obtain a medium effect size for BMR (Cohen’s *d* effect size = 0.3) [54]. Using standardized and customized screening questionnaires for sleep quality and general health, volunteers will be screened to ensure that they are free from any chronic illness, depression, sleep disorders, for at least 6 months prior to the start of the study. Volunteers will be excluded if they are overweight or obese (BMI ≥ 26 kg/m^2^), have any adverse cardiac or metabolic conditions such as type 1 or 2 diabetes mellitus, hypercholesterolemia or hypertension confirmed by a clinician. The Pittsburgh Sleep Quality Index (PSQI) [55] and the General Health Questionnaire (GHQ) [56] will be used to assess quality of sleep and psychological health, respectively. Eligible participants will be asked to maintain the same level of physical activity throughout the study, which will be monitored using the standardized Global Physical Activity Questionnaire (GPAQ) [57]. If participants are taking a daily vitamin/mineral supplement, they will be asked to continue taking it as usual. If they are not taking any supplement they will be asked not to start taking one during the study. Using the dietary data obtained from 1 week of habitual dietary monitoring at the start of the study, daily calorie intake will be calculated for each participant and the total amount of calories consumed daily during both dietary interventions will be based on this value.

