##### Blood sampling and collection

After an overnight fast (minimum of 10 h) a 10-ml venous blood sample will be drawn by venous puncture from the brachial vein of the participant for the assessment of biomarkers of cardiovascular and metabolic health. These biomarkers include lipid profiles (concentrations of triglycerides, LDL, HDL and total cholesterol), interleukin-6 (IL-6), interleukin-1 (IL-1), high-sensitivity C-reactive protein (hsCRP), tumor necrosis factor alpha (TNF-α), ferritin, and serum amyloid P. The blood sample will also be used to assess thyroid function by measuring levels of thyroid stimulating hormone (TSH), T3 and T4. Blood samples will be taken before and after both dietary interventions. Samples will be analyzed by a reputable external laboratory (Clinical Laboratory Service, Johannesburg, South Africa).

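### In its standard form, the repeated-measures ANOVA named for every outcome drops a participant who lacks any one of the four values; a suitable mixed model would keep the rest

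*Protocol article*

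**What the plan says.** The Data analysis section fixes one method for all outcomes, to be run in SPSS version 24: "using a repeated-measures two-way analysis of variance (ANOVA"). It names the factors as follows: "Each outcome variable assessed will be analyzed according to diet (KD or HCLF) and time (before and after each diet"). Diet has two levels and time has two, so each person has four cells.

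The data under that model are described in two other sections. Laboratory assessments: "Before and after each dietary intervention (i.e., four times), participants will return to the laboratory after an overnight fast". Blood sampling and collection: "Blood samples will be taken before and after both dietary interventions".

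The Participants section sets the size: "Twenty healthy individuals, between the ages of 18 and 50 years, will be asked to volunteer in this study". The power statement there and under Data analysis mentions no allowance for loss. The article states no expected missingness rate, no expected number of completers and no rule for incomplete participants.

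**The concern.** In the usual one-row-per-person layout, a two-way repeated-measures ANOVA needs a value in all four diet-by-time cells. A person with three of the four values leaves that outcome's analysis, and someone who stops after the first diet contributes nothing. The number analysed can then differ from one outcome to the next.

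Some incomplete data are foreseeable. Each person faces two diets of at least three weeks, a washout, four fasting visits, several blood assays and a computerised cognitive battery. The Study design section also provides for removing participants during the ketogenic diet. If that diet comes second, such a person may already have three laboratory visits.

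Two things are at stake. The first is power that could have been kept in a trial of 20. The second is possible bias when missingness depends on values already observed, for example when a poor result on the first diet leads to withdrawal. A likelihood-based model handles that case under missing at random; a complete-case analysis generally does not.

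**Working it through.** **The plan's own figure.** The article gives no number of analysed participants to reproduce. Its only related figure is the power statement: "A total of 20 participants would provide 85% power to obtain a medium effect size for BMR", with Cohen's d = 0.3. A two-sided paired t test with n = 20 and d = 0.3 has 24.7% power, so 85% does not follow from the stated inputs on that reading. That is a separate matter and nothing below rests on it. The reference effect used here is one with 80% power in 20 complete participants.

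**Inputs from the article.** 20 participants; four values per person and outcome; two-sided test ("A two-tailed statistical significance will be accepted at" P < 0.05).

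**Assumed inputs, not in the article.** Probability p that a value is missing at a visit, 1% to 10%, independent across visits. Within-person correlation: either equal across all four visits (0.5 to 0.9), or higher within a diet period than across periods.

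**Step 1: complete cases.** Expected number = 20 × (1 − p)^4.

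- 1%: 20 × 0.99^4 = 19.2
- 3%: 20 × 0.97^4 = 17.7
- 5%: 20 × 0.95^4 = 16.3
- 10%: 20 × 0.90^4 = 13.1

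Even at 1%, the chance that all 20 people are complete for an outcome is 0.99^80 = 45%.

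**Step 2: effective sample when all visits are used.** For each pattern of observed visits, the information is X′V⁻¹X restricted to those visits. It is averaged over patterns with their probabilities and inverted for the diet-by-time term. Effective n = 20 × (variance with complete data ÷ variance with missing data).

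| Missing per visit | Complete cases | Effective n, all visits |
|---|---|---|
| 5% | 16.3 | 18.2–18.8 |
| 10% | 13.1 | 16.5–17.5 |

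The upper ends come from equal correlation. The lower ends come from stronger correlation within a diet period than across periods.

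**Step 3: withdrawal after the first diet.** Suppose 4 of 20 stop then, two on each diet. Each diet's change is then observed in 18 people. If a person's two changes are uncorrelated, the variance of their difference is proportional to 1/18 + 1/18, the same as for 18 full completers. The ANOVA keeps 16.

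**Step 4: power.** A paired t test with 80% power at n = 20 needs a standardised difference of about 0.66. At n = 16 its power is 69.5%, and at n = 13 it is 59%. Simulations with 20 participants agree:

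| Missing per visit | ANOVA, complete cases | Mixed model, all visits |
|---|---|---|
| 5% | about 70% | 78–80% |
| 10% | 57–60% | 75–76% |

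Part of the mixed model's gain comes from pooled error degrees of freedom rather than recovered data. With nothing missing and equal correlation, a random-intercept model already had 82% against 79% in simulation.

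**Step 5: which mixed model.** Take correlation 0.8 within a diet period and 0.6 across (assumed), with unit variance. The two change scores are uncorrelated, so the diet-by-time contrast has variance 4 × (1 − 0.8) = 0.80 per person. A participant intercept alone assumes one common correlation, here about (2 × 0.8 + 4 × 0.6)/6 = 0.667, and so uses 4 × (1 − 0.667) = 1.33. That is 1.67 times too large. In simulation with no missing data its power was 67% against 82% for the ANOVA, with type I error near 2%. Adding a participant-by-diet-period random effect gave 83% with none missing, 78% against 70% at 5% missing, and 76% against 60% at 10%, with type I error about 4–6%.

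**The case against.** The strongest reply is that the article names a model and a package but no data layout, analysis set or missing-value rule. An ANOVA with one row per visit and participant as a blocking factor keeps incomplete people. In simulation with equal correlation 0.7 it reached 79% power at 5% missing and 77% at 10%. A statistical analysis plan that is not shown could also specify imputation. This stands in part: the article does not prescribe complete-case analysis in words, and the point concerns the named method in its standard form. But that method is fixed in the text, and the blocking version is the random-intercept analysis in another form. With complete data its diet-by-time test is the same, and it shares the weakness in step 5.

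Three stronger readings are tempting and not supported.

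- *The analysis will have 16 or 13 people.* Those figures need about 5% or 10% independent loss per visit. No rate is documented, and the planned daily feedback may keep losses low. Missingness clustered within people would leave more complete cases at the same rate.
- *A failed blood sample removes the person from everything.* Outcomes are analysed one by one, so sleep, cognition and BMR are unaffected.
- *The complete-case estimate is unbiased only if data are missing completely at random.* The contrast is within person. Missingness that depends on a stable characteristic shifting all four values equally cancels out. The exposure to bias is narrower: missingness that depends on earlier observed values.

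It is also fair that a mixed model is not automatically better. With a participant intercept alone it can do worse than the ANOVA, so the covariance structure is part of the recommendation.

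**Conclusion.** The point holds in conditional form. The named ANOVA, as normally run, discards usable data from any participant incomplete on an outcome, and a concrete alternative retains most of it. At 5% missing per visit the difference is 16.3 against 18.2–18.8 effective participants, or roughly 8 to 10 points of power. At 10% it is 13.1 against 16.5–17.5, or roughly 15 to 19 points. At 1% the ANOVA still keeps about 19 of 20 and little is lost.

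These sizes rest on assumed independent missingness, assumed correlations and a reference effect with 80% power; none comes from the article. The mechanism does not depend on them. This is an avoidable inefficiency with some exposure to bias, not an error that invalidates the trial.

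**What to change.** In the Data analysis section, replace the repeated-measures ANOVA by a linear mixed model fitted by REML in SPSS, specified as follows:

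- fixed effects for diet, time and diet-by-time, as now;
- random effects for participant and for participant-by-diet-period, not a participant intercept alone;
- Satterthwaite degrees of freedom, because the sample is small;
- all available visits included for each outcome.

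Report the number of participants and visits contributing to each outcome.

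The cost is analysis wording: no extra visit, sample or participant, and the same software. With complete data the diet-by-time estimate equals that of the ANOVA, though its standard error and test can differ slightly. There are two limits. The covariance structure must be pre-specified, and little is recovered for a person with no post-diet value. The change leaves the rules for removing participants during the ketogenic diet as they are.

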A controlled, cross-over dietary intervention in healthy individuals, incorporating vital aspects of physiological health into one study and negating the effect of body mass loss and calorie intake, has not yet been done. Given that the majority of studies investigating the KD have: (1) been done in overweight/obese populations, with or without diabetes mellitus and/or insulin resistance, (2) did not control for total caloric intake and levels of physical activity, and (3) did not incorporate a cross-over of subjects doing both diets, this study will account for the many study limitations that exist in the current academic literature by controlling for body mass, existing disease, and calorie intake. Therefore, we wish to determine, in a randomized-controlled cross-over study design, whether a KD, compared with a HCLF diet, affects sleep, cognition, thyroid function, and cardiovascular effects in a generally healthy, non-obese/overweight population while maintaining body mass on the two diets. In addition, we aim to determine whether BMR is different between the ketogenic and HCLF diets in normal healthy adults and whether this difference is associated with any difference in sleep, cognitive and cardiovascular physiology.

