Weight loss is an outcome measure of most studies; however, mechanisms to explain potential changes in weight are poorly explored and the observed weight loss is often used to explain other effects on physiological health [6–8]. Despite a large number of studies investigating the effects of diet on weight loss, the effect of diet on thyroid function and BMR is poorly understood. Following short-term and sustained weight loss, adaptive thermogenesis occurs, where total energy expenditure, non-resting energy expenditure and resting energy expenditure, are all significantly reduced compared with pre-weight-loss measures [52]. Thus, the decline in overall energy expenditure, favors the regain of the lost weight, and this metabolic compensation persists well beyond the period of active weight loss [38]. BMR is the largest contributor of total daily energy expenditure but is known to be the least modifiable component [61]. Exercise-associated thermogenesis (EAT), non-exercise-associate thermogenesis (NEAT), and TEF (the thermic effect of food) constitute the three components of the more changeable components of metabolism, and are known collectively as NREE (non-resting energy expenditure). Given that NEAT (i.e., non-structured exercise, including walking, standing, fidgeting, doing housework, etc.) is the largest component of the changeable aspects of metabolism, and given that metabolic compensation following weight loss largely targets NEAT, but may also modify your motivation to exercise (EAT), in this study we wish to reduce these confounders by (1) monitoring physical activity levels, but also, more importantly, (2) implementing a dietary intervention without a calorie deficit. In particular, each dietary intervention (macronutrient composition) will be designed according to each participant’s habitual daily calorie consumption. The purpose is to mitigate a change in body mass and, therefore, the associated changes in metabolism, in order to determine whether dietary macronutrient composition alone (i.e., changes in the relative contribution of each macronutrient consumed daily, without changing total calorie intake) can affect metabolic rate, and related thyroid function.

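### Choosing adjustment covariates by regression on the trial's own data (planned N = 20) removes little bias from a cross-over contrast, and can raise the false-positive rate or change what is estimated

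*Protocol article*

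**What the plan says.** The Study design section reads: "The design of the study is a randomized controlled, cross-over trial". Each participant follows both diets in random order.

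Under Data analysis, "Each outcome variable assessed will be analyzed according to diet (KD or HCLF) and time (before and after each diet"), using a two-way repeated-measures ANOVA. The test level is given as "A two-tailed statistical significance will be accepted at *P* < 0.05". The adjustment rule then follows: "Variables will be adjusted for potential confounders which will be determined using multiple linear regressions". No covariate is named, no limit is set on when a covariate may be measured, and the unadjusted comparison is not given precedence.

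Two other places show which variables could become candidates. On activity-related energy expenditure, the Discussion says "in this study we wish to reduce these confounders by (1) monitoring physical activity levels". The Background plans to ask, of the BMR difference between diets, "whether this difference is associated with any difference in sleep, cognitive and cardiovascular physiology". The article also has body mass, calorie intake, ketones, mood and weekly physical activity recorded during or after each diet.

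**The concern.** The rule lets the data decide, possibly differently for each outcome, what the diet comparison is adjusted for. Three things are at stake.

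- **Purpose.** Confounder screening belongs to comparisons between different people. Here the comparison is within person and randomised in order, so there is little for it to remove.
- **Error rate.** Choosing covariates by their fit in a sample of about 20, then testing diet in the same sample as if the model had been fixed, need not keep the 5% level.
- **Estimand.** The covariates that can move a within-person contrast are those that vary between periods. Many of these are measured after allocation, and the diet may change them. Adjusting for such a variable replaces the total change due to diet, which the Outcomes section makes primary, with some other quantity.

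**Working it through.** **Inputs from the article:** 20 participants, two-sided 0.05, each participant on both diets. **Assumed, because not stated:** 3 to 10 candidates, entry at p<0.05 or p<0.10, candidates unrelated to the outcome, and mean differences between diets of 0 to 1.5 SD.

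The only design figure in the section is "A power analysis has indicated that total of 20 participants would provide 85% power to obtain a medium effect size for BMR" ("effect size = 0.3"). Read as a standardised within-person difference, 0.3 gives 24.7% power in a two-sided paired t-test with n = 20, so 85% is not reproduced on that reading. This is a separate matter, and nothing below uses it.

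**Step 1: fixed traits.** Write the outcome of person i on a diet as α_i + γz_i + δ·[KD] + error, where z_i is a fixed trait. The within-person difference is D_i = δ + (error on KD − error on HCLF), so α_i and γz_i drop out. In a simulated set of 20 complete pairs, the diet estimate was 0.538 without the trait, 0.538 with it, and 0.538 with participant effects.

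**Step 2: selection, with no true diet effect.** Regress D_i on the K covariate differences x_ik (KD minus HCLF), keep those below the entry level, refit and test the intercept. The estimate is mean(D) − Σ b_k·mean(x_k). Selection keeps coefficients b_k that are large by chance. When mean(x_k) is far from zero, their product moves the estimate, and the standard error ignores the selection. With centred covariates mean(x_k) = 0, so the estimate stays at mean(D) and only the residual variance is understated.

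The table gives rejection rates at 0.05 from repeated independent runs of 5,000 trials per case. The simulation standard error near 5% is √(0.05 × 0.95 / 5000) = 0.3 points.

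| Candidates | Shift between diets | Entry p | Uncentred | Centred |
|---|---|---|---|---|
| 3 to 8 | none | <0.05 | 5.1-7.1% | – |
| 3, one shifted | 0.3 SD | <0.05 | 5.1% | – |
| 6, two shifted | 0.3 SD | <0.05 | 6.0% | – |
| 6, all shifted | 0.3 SD | <0.05 | 7.6% | – |
| 6, two shifted | 1 SD | <0.05 | 8.1-9.7% | 5.4% |
| 6, all shifted | 1 SD | <0.05 | 12.0-12.9% | 6.3% |
| 8, four shifted | 1.5 SD | <0.05 | 11.2-12.4% | 6.3% |
| 8, four shifted | 1.5 SD | <0.10 | 15.3-17.6% | 7.4% |

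Without selection the rate was 4.5-5.3%. A separate set with pure-noise candidates, full-model or forward selection and entry at 0.05 or 0.10 (1,500 runs per case, standard error 0.6 points) gave these rates:

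- 3 candidates: 4.5-6.3%
- 5 candidates: 5.6-7.3%
- 8 to 10 candidates: 6.1-9.7%, with the highest values at entry p<0.10

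**Step 3: adjusting for a variable the diet changes.** Let the diet shift a variable by a, let that variable shift the outcome by b, and let c be the direct effect. The total effect is ab + c, and the adjusted estimate targets c.

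- 0.5 × 0.5 + 0.45 = 0.70: adjusted estimate 0.45; power falls from 85% to 49%.
- 0.7 × 0.6 + 0.28 = 0.70: adjusted estimate 0.28; power falls from 84% to 21%.
- 1 × 0.7 + 0 = 0.70: adjusted estimate 0; power falls from 84% to 6%.

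These results follow from the chosen a, b and c. They show the mechanism and are not a forecast for this trial.

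**The case against.** **The inflation may be small.** The higher rates need several candidates that differ strongly between diets, yet the design works against that: calories are matched, participants are asked to keep their activity constant, and stable body mass is intended. With 3 unshifted candidates the rise is within simulation error, and with centred covariates even the shifted cases give 5.4-7.4%. This stands. A reader might infer that the 5% level will be badly breached, but the article does not give the inputs that would show it.

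**No covariate measured during the diets is named.** This also stands. A reader might infer that the diet effect will be adjusted away, but the text only permits this. The nearest it comes is the Discussion, which treats activity as a confounder. If only fixed traits were selected, the paired estimate would not move.

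**The trial asks about effects apart from weight loss.** Adjusting for a residual change in body mass serves that question, so it would be wrong to rule out all adjustment for variables measured after allocation. This supports one planned analysis. It does not support screening outcome by outcome.

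**A cross-over is not immune to confounding between people.** One might say it has none at all. The Study design section, however, excludes participants after randomisation for failing to reach or hold ketosis. Fixed traits cancel only in pairs with both periods observed. The qualification is right, but regression screening does not repair those exclusions.

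**An analysis plan may hold the covariate list and entry rule.** Their absence from the article is therefore not held against it. The point is the principle that the article does state.

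**Conclusion.** The point holds in a limited form. The article commits to choosing covariates by regression, and by its own account the only data available are the trial's. For complete pairs this removes little bias. Period differences can remain, but a period term deals with those and screening does not.

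The cost per outcome is a false-positive rate of roughly 5-7% under mild assumptions. It is about 9-13% with several strongly shifted, uncentred candidates, and about 15-18% if entry is at p<0.10. The upper figures are the unfavourable end of unstated conditions. Separately, selecting a variable that the diet changes would alter what is estimated, by an amount that the article does not allow anyone to calculate. Outcomes could also end up adjusted for different, partly chance-selected variables, which makes them hard to compare. The sentence should be changed, but nothing here shows that the trial's results will be wrong.

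**What to change.** Replace the sentence with one prespecified primary model for all outcomes: diet, period and sequence as fixed effects and participant as random. Any covariates should be named in advance and limited to values measured before each diet, such as the outcome's own pre-diet value. State that no covariate is chosen by significance.

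Report adjustment for change in body mass, which addresses the question about effects apart from weight loss, as a prespecified and labelled secondary analysis. Treat any other variable measured during the diets, such as activity, in the same way.

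The cost is wording only: no visit, measurement or participant changes, and there is less model building to do. The secondary body-mass analysis needs cautious reading because body mass is measured after allocation.
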